## Design.

A monocenter prospective, exploratory study with a 1 to 2-week screening period and a 52-week follow-up period in 120 RA patients who receive adalimumab treatment in routine rheumatological practice and are TNF- blockade naïve or have failed to (or no longer) respond to other anti-TNF- treatment. There is no group of patients receiving control treatment, since it is considered unethical to withhold active treatment for 52 weeks in patients with active RA. Previous work has shown the efficacy of adalimumab in randomized trials (8;9).

The goal of the present study is to evaluate the response to adalimumab treatment in the TNF- blockade naïve patients and patients who failed on other prior TNF- blocking treatment. Therefore, responders will be compared with non-responders after all included patients have received anti-TNF- therapy in the form of adalimumab. Furthermore the goal is to understand more of the mechanisms underlying the response to anti-TNF- treatment. Adalimumab treatment will be discontinued in patients who do not fulfill the Eular response criteria for improvement (DAS 28) at week 16, according to routine clinical practice.

Patients who discontinue adalimumab at or after week 16 for lack of respons or other reasons will get a final clinical assessment as part of the close out visit. The reason for discontinuation will be noted in the case record form. These patients will not be followed for measurement of clinical parameters. In patients who respond, treatment will be continued and may be extended after the 52-week follow-up period of this study. Patients will be included starting January 2004.

Patients who drop out of the study before week 16 for any reason will be replaced by new patients, the reason of discontiuation will be noted in the case record form (*see withdrawl and replacement of patients)*

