## Duration of study

All patients participating in this study will receive 40 mg (0,8ml) adalimumab by subcutaneous injection every other week after fulfilling all inclusion criteria at baseline. All patients must have approval for reimbursement for TNF-blockade by their insurance company (DAS 28 >3.2). Patients will be seen during the study for efficacy and safety assessments at weeks 4, 16, 28, 40 and 52 using validated and generally accepted evaluation criteria (see laboratory and clinical variables). All visits will be fixed with reference to the baseline visit. Evaluation of ACR 20 and Eular response (DAS 28) will be performed at 16 weeks after initiation of adalimumab. The final clinical assessments will be performed at 52 weeks. If the patient does not meet the Eular criteria for moderate or good response at 16 weeks, adalimumab treatment is discontinued and no further assessments will be done.

Inclusion criteria:

1) Patients with the diagnosis rheumatoid arthritis according to the American Rheumatism Association (ARA) 1987 criteria and in ACR 1991 functional classes I, II, and III *(see appendix)*

2) The patient is naïve for anti-TNF- therapy or has failed other prior TNF- blockers

3) DAS 28  3.2

4) Age > 18 and  85 years old

5) Use concurrent methotrexate treatment (5 - 30 mg/week; stable since at least 28

days before initiation) during the study. Subjects may be taking nonsteroidal anti-

inflammatory drugs, provided the dose and frequency have been stable for at

least 28 days. Subjects may be receiving prednisone therapy  10 mg/day

provided that the dosage has been stable for at least 2 months prior to entry.

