Serious and opportunistic infections have been described in patients receiving TNF blocking agents, but it is not clear that their incidence is higher than in patients with rheumatoid arthritis using other forms of DMARD therapy and/or corticosteroids. TNF blocking agents should not be started or should be discontinued when serious infections occur, including septic arthritis, infected prostheses, acute abscess, osteomyelitis, sepsis, systemic fungal infections, Listeria etc. Treatment with TNF-blockers in such patients should only be resumed if the infections have been treated adequately.

Pregnancy

An embryo-fetal perinatal developmental toxicity study has been performed in monkeys and has revealed no evidence of harm to the fetuses due to adalimumab, however no adequate and well-controlled studies in pregnant women have been performed. For this reason pregnancy is an exclusion criterium in this study.

Overdosage

The maximum tolerated dosage of adalimumab has not been established in humans. Multiple doses up to 10mg/kg have been administered to patients in clinical trials without evidense of dose-limiting toxicities. In case of an overdosage, the patient will be monitored for any signs or symptoms of adverse reactions or effects and treated when necessary.

Adverse events

An adverse event is any event which impairs the wellbeing of the patient during the period of observation in a clinical study, including intercur­rent illness or accident. The term ad­verse event does not imply a causal re­lation­ship with the study treat­ment.

The period of observation for adverse events extends from the time the patient gives informed consent until he or she undergoes a final exami­nation as part of the study, including periods before and after an active treatment phase during which no drug or other treatment is given. The period may also include a specified number of days after the final ex­amination during which time serious adverse events must be re­ported (see below). Adverse events occurring after the end of the study must be re­ported if the investigator considers there is a causal relationship with the study medica­tion.

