All patients experiencing adverse events ‑ whether considered as­soci­ated[[1]](#footnote-2) with the use of the study medication or not ‑ must be monitored until symptoms subside and any abnormal laboratory values have re­turned to baseline, or until there is a satis­factory explanation for the changes ob­served, or until death, in which case a full pathologist's re­port should be supplied, if possible. All findings must be reported in the patient's medi­cal re­cords.

All drug-related adverse events, including intercurrent illnesses, must be reported on and docu­mented as described below.

Adverse events are divided into the categories "serious" and "non­seri­ous". This determines the procedure that must be used to re­port/document the adverse event (see below).

*Definition of serious and non-serious adverse events*

A serious adverse event is any adverse event occurring at any dose that results in:

1. Death
2. A life-threatening event
3. Inpatient hospitalization or prolongation of existing hospitalization
4. Persistent or significant disability/incapacity
5. Congenital anomaly/birth defect

Adverse events that do not fall into these categories are defined as non-serious.

*Reporting/documentation of adverse events*

*Serious adverse events*

All serious adverse events which occur during the period of observation, whether consid­ered to be associated with the study medication or not must also be docu­mented in the case record form.

Where necessary, inves­tigators will in­form the medical ethics committee and authorities.

*Non-serious adverse events*

These are to be documented in the case re­cord form if related with the study medication.

*Adverse events occurring after the period of observation*

Any adverse event occurring at any time after the end of the study and considered to be caused by the study medication - and therefore a possible adverse drug reac­tion - must be re­ported as above.

*Assessment of severity*

Regardless of the classification of an adverse event as serious or non-se­ri­ous (see above), its severity must be assessed as mild, moderate or se­vere, according to medical criteria alone:

mild = does not interfere with routine activities

moderate = interferes with routine activities

severe = impossible to perform routine activities

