### Withdrawl and replacement of patients

Patients who drop out of the study before week 16 for any reason will be replaced by new patients, the reason of discontiuation will be noted in the case record form.

These patients will be seen for a final clinical assessment as part of the close out visit.

This visit will include physical examination, final assessment of disease activity (ACR, DAS 28, RADAI, SF 36), follow up of previous adverse events. Blood will be drawn for safety screening of clinical heamatology and chemistry parameters. Furthermore final immuno- serology to screen for auto-antibody formation (ANA, anti-ds DNA). Titers of IgM-RF and anti-CCP will also be drawn at this visit.

Premature discontinuation of study

The investigator has the right to discontinue this study at any time for medical and/or administrative reasons. As far as possible, this should occur after mutual consultation. Furthermore adalimumab treatment will be discontinued if there is no reimbursement by the insurance company.

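### As written, all-cause recording of serious adverse events ends at close-out, with no fixed window after adalimumab is stopped

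*Protocol*

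**What the plan says.** Four parts of the protocol's Section 2 bear on this.

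- **Adverse events.** Observation runs from consent to the final examination and counts untreated periods before and after active treatment. For serious events it adds "The period may also include a specified number of days after the final" examination and points the reader further down. Neither the following text nor any other section gives a number. Events after the end of the study must be reported "if the investigator considers there is a causal relationship with the study" medication. The same section requires adverse events to be monitored until they settle or are explained.
- **Reporting/documentation of adverse events.** The duty to document whatever the cause covers "All serious adverse events which occur during the period of observation". Afterwards the duty is limited to "Any adverse event occurring at any time after the end of the study and considered to be caused by the study medication".
- **Duration of study.** For patients without a moderate or good EULAR response at week 16, "adalimumab treatment is discontinued and no further assessments will be done".
- **Design.** "Patients who discontinue adalimumab at or after week 16 for lack of respons or other reasons will get a final clinical assessment" at a close-out visit, and then "These patients will not be followed for measurement of clinical parameters". No date for close-out is given.

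The Withdrawal and replacement section describes the content of a close-out visit for earlier drop-outs. It includes "follow up of previous adverse events", which looks back, not forward.

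**The concern.** How long serious events are collected is a protocol matter. An analysis plan cannot recover events that were never recorded, so this cannot be left to one.

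Read together, the rules make all-cause capture after week 16 depend on response. Take a new serious infection at week 20. In a responder still in the study it is documented whatever the cause. In a week-16 non-responder whose close-out has passed, it is recorded only if the investigator hears of it, with no study contact planned, and then attributes it to adalimumab. Attribution is a weak filter here: there is no control group, and the Infections section itself regards it as unclear whether TNF blockers raise the incidence of serious infection.

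There is also a conflict of wording. An order for no further assessments at week 16 sits badly with the duty to follow open adverse events until they resolve.

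**Working it through.** The protocol states no figure for this interval, so there is nothing to reproduce. The check is calendar arithmetic followed by an illustration of size.

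**Inputs from the protocol**
- Doses at baseline and every 14 days (Study medication and dosage), so doses fall on days 84, 98 and 112.
- Visit tolerance of 7 days either way (same section), so the week-16 visit falls on days 105 to 119.
- One dosing break of at most 10 days, in the context of surgery under general anaesthesia (Concomitant medications).
- Planned sample of 120 patients (Design).

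**Assumptions**
- Close-out is the week-16 visit.
- The dose due that day is either given or held for the response decision. The protocol does not say which.

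**Step 1. Days from last dose to close-out (visit day minus last dose day)**

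| Week-16 visit | Day-112 dose given | Day-112 dose held |
| --- | --- | --- |
| Day 112 | 112 − 112 = 0 | 112 − 98 = 14 |
| Days 105 to 119 | 0 to 13 | 7 (105 − 98) to 21 (119 − 98) |

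The range is therefore 0 to 14 days on schedule and 0 to 21 days with the visit tolerance.

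**Step 2. Effect of a permitted interruption.** Suppose the day-98 dose is postponed by 10 days to day 108 and then held until the visit, so that the last dose was on day 84. A visit on day 108 gives 108 − 84 = 24 days, on day 112 it gives 28, and on day 119 it gives 35. These are examples, not a bound.

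**Step 3. The comparison.** A responder who completes has (52 − 16) × 7 = 252 further days of all-cause capture. A responder who stops between weeks 16 and 52 goes to close-out like any other stopper and has fewer.

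**Step 4. Size, as illustration only.** A window of W days after the last dose adds W − 14 to W days per stopper on schedule. Assume 36 stoppers (30% of 120; the Introduction gives at least 30% non-response for infliximab, assumed here to carry over) and 0.05 to 0.2 new serious events per patient-year (assumed).

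| W | Days added per stopper | Patient-years (36 × days / 365.25) | Events |
| --- | --- | --- | --- |
| 30 | 16 to 30 | 1.58 to 2.96 | 1.58 × 0.05 = 0.08 to 2.96 × 0.2 = 0.6 |
| 60 | 46 to 60 | 4.53 to 5.91 | 4.53 × 0.05 = 0.2 to 5.91 × 0.2 = 1.2 |
| 90 | 76 to 90 | 7.49 to 8.87 | 7.49 × 0.05 = 0.4 to 8.87 × 0.2 = 1.8 |

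**The case against.** The strongest reply is that the default is not blank. The protocol fixes the end of observation at the final examination, and the extension is merely permissive, so what remains is an unused template sentence. That is right as a reading of the text: no promised window is broken. It does not remove the consequence, because an extension without a number gives no window in practice.

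Second, the loss is narrow. Drug-attributed events stay reportable without time limit, the footnote on association asks only for a reasonable possibility, and open events are followed. Patients come from routine practice at one centre, and nothing says that ordinary care ends at close-out. The Concomitant illnesses section also treats illnesses in the study period as adverse events without a causality test, although it does not say whether that period outlasts close-out. All of this stands and limits the gap to new serious events that are judged unrelated or never reach the investigator.

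Third, the timing depends on an assumed close-out date, and observation is said to include untreated periods after therapy. This also stands. A later close-out would lengthen capture, but the protocol does not require one.

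A reader might go further and infer that safety reporting stops altogether at week 16, that the interval has a definite maximum, or that the imbalance biases the response or marker results. The documents support none of these. Attributed and open events remain covered. Step 2 shows that the gap grows with how doses are held. The primary endpoint is fixed at week 16, and no safety comparison by response is planned.

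**Conclusion.** The point holds as a minor one. No all-cause serious-event window applies after close-out, and the week-16 instruction in Duration of study is worded more broadly than the Design section and the duty to follow open events allow.

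The timing (0 to 14 days on schedule, up to 21 with the visit tolerance, longer after an interruption) rests on close-out being the week-16 visit. The stopper count, event rates and window lengths are assumptions. Under them a 60-day window would pick up about 0.2 to 1.2 events. The case for acting is that such events cannot be recovered later and the remedy costs little, not that many are expected.

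**What to change.** 1. In Adverse events, replace the optional sentence with: *For every patient who stops adalimumab during the study, at any time and for any reason, all serious adverse events are recorded whatever the cause until 60 days after the last dose, with one telephone contact at that time.* Sixty days is pragmatic. It matches the wash-out for monoclonal antibodies in exclusion criterion 5 and is not a derived carry-over period; the protocol gives no half-life from which to derive one. The sponsor may substitute a pharmacologically based figure.
2. In Duration of study, limit the week-16 instruction to *no further efficacy assessments*. This fits the narrower wording in Design and the duty to follow open events.
3. In Safety Variables, extend the separate infection, malignancy and hospitalisation page, now tied to time on adalimumab, to the same window. Without this the new rule creates a fresh inconsistency.
4. Record the start date of any next biological.

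Cost: one call per stopper (36 if 30% stop; 12 to 60 at an assumed 10% to 50% of 120), three wording changes and one form field. The downside is that some events will fall after a next biological has started and will need a flag.

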### Withdrawl and replacement of patients

Patients who drop out of the study before week 16 for any reason will be replaced by new patients, the reason of discontiuation will be noted in the case record form.

These patients will be seen for a final clinical assessment as part of the close out visit.

This visit will include physical examination, final assessment of disease activity (ACR, DAS 28, RADAI, SF 36), follow up of previous adverse events. Blood will be drawn for safety screening of clinical heamatology and chemistry parameters. Furthermore final immuno- serology to screen for auto-antibody formation (ANA, anti-ds DNA). Titers of IgM-RF and anti-CCP will also be drawn at this visit.

Premature discontinuation of study

The investigator has the right to discontinue this study at any time for medical and/or administrative reasons. As far as possible, this should occur after mutual consultation. Furthermore adalimumab treatment will be discontinued if there is no reimbursement by the insurance company.

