### Primary endpoint

The primary endpoint of the study is the percentage of patients with a moderate to good response to adalimumab treatment at 16 weeks according to the Eular response criteria which is also applied in routine rheumatological practice.

A decrease in the DAS 28 value must be ≥ 1.2 at any given timepoint after initiation of treatment for continuation of reimbursement by the insurance company.

| **DAS 28 score at**  **(week 16)** | **Improvement in DAS 28 at week 16 compared to baseline (week 0)** | | |
| --- | --- | --- | --- |
|  | **>1.2** | **> 0.6 en  1.2** | ** 0.6** |
| ** 3.2** | **Good** |  |  |
| **> 3.2**  **and  5.1** |  | **Moderate** |  |
| **> 5.1** |  |  | **None** |

*Tabel 1: Eular response criteria*

Furthermore the primary endpoint of the study is to search for clinical parameters and/or serological markers that possibly distinguish responders from non-responders to TNF-α blockade by adalimumab.

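### Patients lost before week 16 are replaced and nothing keeps them in the primary percentage, so on its ordinary reading the rate is biased upward unless drop-outs respond like completers

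*Protocol*

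**What the plan says.** The Design section describes a single-centre exploratory study "in 120 RA patients who receive adalimumab treatment in routine rheumatological practice", without a control group. The Primary endpoint section defines the first part of the endpoint as "the percentage of patients with a moderate to good response to adalimumab treatment at 16 weeks according to the Eular response criteria". The second part is a search for clinical or serological features that separate responders from non-responders.

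The replacement rule appears in the same words under Design and under Withdrawal and replacement of patients: "Patients who drop out of the study before week 16 for any reason will be replaced by new patients". The reason for leaving goes into the case record form. The withdrawal section adds: "These patients will be seen for a final clinical assessment as part of the close out visit". That visit includes the DAS 28.

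Patients who stop at or after week 16 are treated differently. Under Design they have a close-out visit, and no replacement is mentioned for them.

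The Data analysis section describes the proportion responding by prior anti-TNF status and plans a logistic regression for predictors of response. It does not say how replaced patients enter either analysis.

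**The concern.** The replacement cut-off coincides with the primary time point. If a replaced patient is simply exchanged for a new one, the 120 patients behind the percentage are those who stayed to be assessed. Some reasons for leaving early are related to outcome. Intolerance and perceived lack of effect are covered by the rule, and the Infections section calls for stopping TNF blockers when a serious infection occurs. Selecting on arrival at week 16 is then partly selecting on response.

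Three results are exposed:

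- the primary percentage itself;
- the comparison of TNF-blocker-naïve patients with prior failures (research question 2), if early drop-out differs between the groups;
- the marker comparison and the logistic model, because the non-responder group would lack patients who left early.

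**Working it through.** The protocol gives 120 patients without an expected response, drop-out rate, power or precision target, so it has no figure of its own to reproduce. The check is how far the completer rate can lie above the all-treated rate.

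**Inputs**

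- From the protocol: N = 120 (Design); replacement of all drop-outs before week 16.
- Assumed: d, the share of enrolled patients who drop out before week 16 (5–20%); p, the response among the 120 who reach week 16 (50–80%); q, the response that drop-outs would have had (0, 25%, or equal to p).

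**Formulas**

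- Enrolled: M = 120/(1 − d), rounded up.
- All-treated response: (120p + q(M − 120))/M.
- Overstatement: p minus that value, which equals (p − q)(M − 120)/M.

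**Enrolment needed**

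- d = 5%: 120/0.95, so M = 127, 7 replaced.
- d = 10%: 120/0.90, so M = 134, 14 replaced.
- d = 15%: 120/0.85, so M = 142, 22 replaced.
- d = 20%: 120/0.80, so M = 150, 30 replaced.

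Worked example with p = 70%, d = 10%, q = 0: 84 responders out of 134 is 62.7%, against 84 out of 120, which is 70%. The gap is 7.3 points.

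**Overstatement in percentage points** (first figure q = 0, second figure q = 25%)

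| p among completers | d = 5% | d = 10% | d = 15% | d = 20% |
|---|---|---|---|---|
| 50% | 2.8 / 1.4 | 5.2 / 2.6 | 7.7 / 3.9 | 10.0 / 5.0 |
| 60% | 3.3 / 1.9 | 6.3 / 3.7 | 9.3 / 5.4 | 12.0 / 7.0 |
| 70% | 3.9 / 2.5 | 7.3 / 4.7 | 10.8 / 7.0 | 14.0 / 9.0 |
| 80% | 4.4 / 3.0 | 8.4 / 5.7 | 12.4 / 8.5 | 16.0 / 11.0 |

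With q = p the overstatement is zero in every cell.

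**Against sampling error.** The 95% half-width at n = 120 is 1.96 × √(p(1 − p)/120): 8.9, 8.8, 8.2 and 7.2 points at p = 50, 60, 70 and 80%. At p = 70% and q = 0, the overstatement is just under the half-width at 10% drop-out (7.3 against 8.2) and above it at 15% (10.8). At q = 25% it stays below at 15% (7.0) and exceeds it at 20% (9.0).

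**Group contrast.** Assume 60 completers per group, 70% response in both (42 responders each), drop-out of 5% in one group and 20% in the other, and q = 0. Enrolled numbers are 64 and 75. The all-treated rates are 42/64 = 65.6% and 42/75 = 56.0%. The completer analysis shows no difference.

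**Non-responder group.** At p = 70%, d = 10% and q = 0, completers supply 120 − 84 = 36 non-responders and the replaced patients 14 more. The marker comparison would then lack 14 of 50, or 28%.

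**The case against.** The strongest objection is that the denominator is inferred. The text is an enrolment rule, and nowhere does the protocol state that replaced patients leave the analysis. A statistical analysis plan, which was not among the documents reviewed, could count everyone enrolled, and the inflation would then disappear. This stands as a limit on certainty. It does not remove the point: exchanging patients to hold a number ordinarily means that the newcomers take their place, and nothing in the protocol says otherwise.

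Second, selection on outcome may be weaker than it looks. The formal stop for non-response is at week 16; those patients have been assessed and count as non-responders. A reader might also infer that lost reimbursement removes many poor responders early, because the protocol says "A decrease in the DAS 28 value must be ≥ 1.2 at any given timepoint after initiation of treatment" for reimbursement to continue and "adalimumab treatment will be discontinued if there is no reimbursement by the insurance company". The schedule places the insurance request only at screening and week 16, so the documents do not show how often this happens before week 16. Intolerance, serious infection and perceived lack of effect remain.

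Third, a reader might infer from the close-out blood draw ("Blood will be drawn for safety screening of clinical heamatology and chemistry parameters", plus auto-antibodies) that early leavers have no stored serum for the marker work. That is not so. The schedule stores serum at T=-2, T=0 and T=4, so pre-treatment samples are planned for those who start, and a week-4 sample for those still in the study. Only a stored sample at the close-out visit itself is not listed.

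Fourth, the study is exploratory and descriptive, with no test or threshold, and the reason for leaving and the close-out DAS 28 are planned for these patients. This lowers the stakes, but it also means that the better analysis needs almost nothing new.

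**Conclusion.** The point holds. On its ordinary reading, the rule gives a response rate among patients who reached week 16, and that rate is biased upward unless drop-outs would have responded as often as completers.

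Its size cannot be fixed from the protocol. Under assumed 5–20% drop-out and 60–80% completer response, it is about 3–16 points if no drop-out would have responded. If a quarter would have, it is about 1–11 points (over 50–80% completer response). The upper figures should not be read as the expected bias: they combine the highest assumed drop-out with the highest assumed completer response. The group contrast and the marker comparison are affected through the same mechanism, to a degree that depends on who leaves early and why.

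**What to change.** State in the protocol that replacement serves only to top up recruitment. Then:

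- Define the primary denominator as all patients who received at least one dose of adalimumab, both those replaced and their replacements.
- Count drop-outs before week 16 as non-responders in the primary percentage.
- Show two sensitivity analyses: one classifying drop-outs by their close-out DAS 28, and one restricted to patients who reached week 16.
- Report the number replaced and the reasons, by prior anti-TNF group.
- Keep these patients in the responder versus non-responder comparison and in the logistic model.

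The cost is about a paragraph of wording; beyond the replacements already planned, no extra patients are needed. The reported percentage becomes somewhat lower, and patients who leave for reasons unrelated to response are counted conservatively, which the two sensitivity analyses help to show. Storing one serum tube at the existing close-out draw would be a useful but optional addition.
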